### Power calculation

As this is an exploratory study to develop control groups for national post-COVID imaging studies and emerging postinfectious cohorts, power calculation depends on the cohorts being compared. A sample size of 176 subjects will afford 90% power (α significance 5%) to show an increase in the prevalence of cardiac abnormalities based on an estimated 10% prevalence in the control group and 20% in the COVID-positive group, from C-MORE pilot data^77^ and a study examining hospitalised patients.^82^ To account for a 10% dropout rate due to missing or incomplete data, 200 participants will be recruited.

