#### Primary outcome measure

Prevalence of cardiac injury in COVID-19 negative controls.

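### The stated 90% power does not follow from 176 subjects, 10% versus 20% and alpha 5%, because the number of COVID-positive cases, the ratio, the sidedness and the test are not given

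*Protocol article*

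**What the plan says.** The Power calculation section first calls the study exploratory and says that the "power calculation depends on the cohorts being compared". It then gives one set of figures: "A sample size of 176 subjects will afford 90% power (α significance 5%) to show an increase in the prevalence of cardiac abnormalities". The rates are "based on an estimated 10% prevalence in the control group" and "20% in the COVID-positive group". An allowance of 10% for missing or incomplete data takes 176 to 200 participants.

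The Abstract and the Study population section show that COSMIC recruits only COVID-negative controls. Under Aims and objectives, the cases are to come from other national studies, with C-MORE and COVID-HEART named. The article gives neither study's size. The primary outcome measure is "Prevalence of cardiac injury in COVID-19 negative controls", a prevalence in a single group.

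**The concern.** Power for comparing two proportions depends on both group sizes. The article gives one number, 176, without saying whether it is the control group, each group or the total, and it does not say how many cases the controls will face. Nor does it state the sidedness or the test. A reader who takes the obvious equal-group reading cannot recover 90%.

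This figure is the article's only numerical justification for 176, and so for 200. The cohort is meant to be reused as a comparator by several studies. A study that pairs these controls with a modest number of cases could carry the 90% forward, although its chance of missing a true rise from 10% to 20% may be 25% or more.

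**Working it through.** **Inputs from the Power calculation section.** p1 = 0.10 (controls), p2 = 0.20 (cases), difference d = 0.10, alpha 5%, 176 subjects, stated power 90%, dropout 10%.

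**Assumptions, because the article is silent.** Independent groups, no covariate adjustment, pooled two-proportion z-test. Both one-sided and two-sided tests are shown, with alternative formulas where they matter.

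**Formula.** For n controls and m cases, let p̄ = (n·p1 + m·p2)/(n + m), SE0 = √[p̄(1 − p̄)(1/n + 1/m)] and SE1 = √[p1(1 − p1)/n + p2(1 − p2)/m]. Power = Φ[(d − z·SE0)/SE1], with z = 1.960 two-sided or 1.645 one-sided.

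**Step 1: try to reproduce 90% with 176 against 176.**
- p̄ = 0.15; SE0 = √(0.1275 × 2/176) = 0.03806; SE1 = √(0.25/176) = 0.03769.
- Two-sided: (0.10 − 1.960 × 0.03806)/0.03769 = 0.674, so power = **75.0%**.
- One-sided: **83.9%**.
- Two-sided with the arcsine formula: 75.9%.

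**Step 2: other equal-group readings.**

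| Reading | Two-sided | One-sided |
|---|---|---|
| 176 in total (88 vs 88) | 45.9% | 58.5% |
| 176 vs 176 | 75.0% | 83.9% |
| 200 vs 200 (no dropout) | 80.2% | 87.8% |

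None reaches 90%.

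**Step 3: size per group for 90% at 1:1.** n = [z·√(2p̄(1 − p̄)) + 1.282·√(p1(1 − p1) + p2(1 − p2))]²/d².
- Two-sided: (1.960 × √0.255 + 1.282 × √0.25)²/0.01 = 265.9, so 266. Unpooled gives 263, arcsine 261, continuity-corrected 286.
- One-sided: 216.5, so 217 (237 continuity-corrected).

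**Step 4: hold 176 controls and find the cases needed for 90%.**

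| Test | Cases needed |
|---|---|
| Two-sided, unpooled | 364 |
| Two-sided, arcsine | 505 |
| Two-sided, pooled | 596 (about 3.4 per control) |
| Two-sided, continuity-corrected | about 880 (5 per control) |
| One-sided, pooled | 286 |

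**Step 5: power with 176 controls by case number (two-sided, pooled).** 100 cases: 63.5%. 176: 75.0%. 250: 80.8%. 400: 86.6%. 596: 90.0%. 600: 90.1%.

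**Step 6: a one-sample test.** Testing 176 subjects against a fixed rate gives about 96% to 97% two-sided and needs only 122 to 137 subjects, so this does not explain 176 either.

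**Step 7: dropout.** 176/0.9 = 195.6, so 196, and 200 covers it. This step is sound.

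**Step 8: precision of the stated primary outcome.** 10% of 176 is about 18. For 18/176 = 10.2%, the Wilson 95% interval is 6.6% to 15.6%.

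**The case against.** The strongest reply is that the article never says 1:1. Only controls are recruited, the cases come from outside, and the section itself warns that power varies with the comparator. The Discussion mentions one potential comparator, PHOSP-COVID, with 8000 people. A ratio above 3:1 is therefore possible, and with enough cases 90% is reached. All of this stands. A reader might infer that 90% is false or unattainable, or that the article claims it for every comparator; the text supports neither. What remains is that a case number is needed to support any single figure and none is printed. The 8000 does not supply it: PHOSP-COVID is cited there mainly for questionnaire data, and the article gives no number of its members with cardiac MRI.

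A second reply is that the Discussion promises controls matched to the post-COVID cohorts, and a paired analysis is more efficient. By McNemar's formula, 176 pairs reach 90% two-sided if about 17% of pairs are discordant, compared with 0.1 × 0.8 + 0.9 × 0.2 = 26% if pair members were independent. So it would be wrong to say that no formula can give 90% at 1:1. But the article states no pairing and no discordance rate, and the Statistical analysis section describes covariate adjustment between cases and controls, not a paired comparison.

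A third reply is that the exact case number depends on the test. That is correct, so a range is given above and the 596 should not be quoted without its assumptions.

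Finally, the study is exploratory and the article is a condensed account. That would excuse leaving out detail. It does not support a specific power figure that the printed inputs fail to deliver.

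**Conclusion.** The point holds as a failure to follow from stated inputs. With independent groups, 10% versus 20% and alpha 5%, no equal-group reading of 176 gives 90%: the pooled test gives about 75% two-sided or 84% one-sided at 176 per group, and about 46% two-sided if 176 is the total. At 176 per group, two-sided, the chance of missing the assumed difference is 25%, not 10%. Against a larger case cohort 90% can be reached, from about 286 cases (one-sided, pooled) through 364 to 596 (two-sided, unpooled to pooled) and to about 880 with a continuity correction.

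These figures assume an unadjusted comparison and the article's two prevalences. The documents do not show how 176 was obtained, so no claim is made about the source of the discrepancy. The recruitment target of 200 need not change.

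**What to change.** Keep 200 participants and replace the single 90% with power conditional on the comparator, naming test and sidedness. Suggested wording: *For 10% versus 20%, two-sided 5%, pooled two-proportion z-test, 176 evaluable controls give 75% power against 176 cases, 81% against 250, 87% against 400 and 90% against about 600.* Add the expected number of evaluable cases for each planned comparator. If a one-sided or paired analysis is intended, say so and recompute; a paired analysis also needs an assumed discordance rate.

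Because the stated primary outcome is a prevalence in controls, add its precision: *With 176 evaluable controls, an observed prevalence of about 10% (18/176) has a Wilson 95% confidence interval of 6.6% to 15.6%.*

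The cost is wording only, with no extra participants. The stated power becomes less favourable for comparisons with modest-sized cohorts.

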## Discussion

The proposed COSMIC study is of direct clinical relevance to individuals at risk of COVID-19 infection or experiencing post-COVID manifestations. As a control group, it will afford mechanistic insights into the pathophysiology and prognostic implications of multiorgan injury following COVID-19 and potentially following hospitalisation for other novel viral infections. Recent multiorgan imaging studies in post-COVID patients such as C-MORE,^60^ COVER-SCAN (mapping organ health in recovery from COVID-19 disease due to SARS-CoV-2 infection)^83^ and COVID-HEART^33^ have limitations including younger control groups with fewer comorbidities, absence of contrast-enhanced imaging to detect fibrosis/perfusion (eg, in COVER-SCAN) and lack of ethnically and sociodemographically matched controls. The COSMIC study provides a robust, contemporary uninfected control group that will be matched to the post-COVID cohorts for age, comorbidities and sociodemographic factors, with comprehensive multiorgan, vascular and lung imaging. However, challenges are likely to be encountered in recruiting participants with a wide range of comorbidity profiles given the limited pool of subjects without a history of prior COVID-19. Although the presence of nucleocapsid-specific antibodies will be utilised as a marker for previous infection, false negative results may arise from antibody waning. In this study, nucleocapsid antibody testing will be used in conjunction with patient-reported history of COVID-19 and prior antigen testing, but previous asymptomatic infection cannot definitively be excluded.

Importantly, the comprehensive clinical assessment of COVID-19 negative controls through a series of questionnaires evaluating self-reported quality of life, level of frailty, cognitive function, mental health and functional capacity paired with deep imaging phenotyping is unique. The parallel assessment of patients using the PHQ-9, GAD-7, MRC Dyspnoea Scale, MoCA and many others will also provide a control group for UK-wide post-COVID follow-up studies such as PHOSP-COVID—a large multicentre study of 8000 previously hospitalised individuals, currently lacking a well-matched control group. Additionally, COSMIC is collecting data on CT lung and vascular inflammation, thus serving as a control to other studies including C19-RS (COVID-19 radiotranscriptomic signature), ORFAN (The Oxford risk factors and non-invasive imaging study)^84^ and the PHOSP-COVID lung fibrosis working group^85^ which focus on the impact of COVID-19 on vascular inflammation, thrombosis and pulmonary interstitial lung disease.

This meticulous approach will enable improved risk stratification and elucidation of mechanistic drivers contributing to severe disease across diverse populations. For patients with long COVID, this work may promote a better understanding of the mechanisms of persistent symptoms and impaired quality of life. Furthermore, the extensive characterisation and phenotyping of a large cohort of COVID-negative controls, coupled with comprehensive multiorgan imaging and serum storage, will provide an invaluable bioresource to support future research into complex interactions between sociodemographic factors, comorbidities and multiorgan health. Despite the success of the vaccine programme, immune escape and viral resistance to antibody responses (following natural infection or vaccination) are expected to occur due to selection pressures on the virus, and thus the likelihood that COVID-19 will be cured remains low. Consequently, insights gained from the COSMIC study into both acute illness and long COVID will enable better preinfection targeting of preventive measures and individualised therapy in infected patients during potential future pandemics.

## Ethics and dissemination

The study was approved by the National Research Ethics Service Committee East Midlands (REC reference 19/EM/0295) and conducted according to the declaration of Helsinki. COSMIC is registered as an extension of C-MORE on ClinicalTrials.gov (NCT04510025). Trial findings will be published in peer-reviewed journals and disseminated at international conferences and scientific meetings.
